### Concomitant drug therapy

Substance, dose and time of administration for any medication (including traditional remedies) taken during FUP shall, if possible, be recorded in the CRF.

## Medical assessment and blood sampling

- - 1. **Clinical assessment**

The Clinician in charge of each Health facility will instruct all patients to come back for follow up assessment any time if symptoms persist or the condition deteriorates, and always on day 14 (or at any convenient time after day 14). At the time of final follow up patients will receive one insecticide treated net (ITN) free of charge.

4.4.2 Sampling for determining parasitemia

A few drops of blood will be taken from all enrolled patients to determine parasitemia: for confirmation of parasitemia by standard microscopy examination in central laboratory in clinical and for the RDT in the intervention arm. The results of RDT will be provided to the patients before treatment, but the microscopy results will only be available for study analysis purposes. Manufacturer’s Instructions Procedure and a special training session by study supervisor prior to study initiation will assist the study clinical officer to perform Rapid Diagnostic Tests. Blood films will be stained with 3% Giemsa for 30 minutes and asexual parasite density will be calculated by counting 200 white blood cells, assuming the white blood cell count of 8000/mm3. If less than 10 parasites are detected per 200 white blood cells, estimates will be made against another 500 white blood cells.

### Sample labeling

Each sample (RDT and blood slides) will be labeled by using a sharpened pencil the following information:

- Day of sampling eg day 0 (D0)
- the Patient Code consisting of an abbreviation of the study site eg UZ, MY etc. followed by serial number starting with 1
- subject initials

D0

UZ 003

KIM

091106

- date of sampling.

## Adverse events

### Adverse event definition

An adverse event is an unintended, unfavorable sign, symptom, change in laboratory test, disease, or complaint, temporally associated with the use of the pharmaceutical products in the study, whether or not a causal relationship can be established. Note that the definition could include reasons for administration of concomitant medication or clinically relevant changes in laboratory variables. It could also include reasons for referral to a consultant or unscheduled admission to hospital.

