## Design, subjects and methods

### Overall study design

## A multicentre randomized validation study comparing RDT + clinical diagnosis versus clinical diagnosis alone in the management of uncomplicated malaria.

### Inclusion criteria

## Any patient attending the study site and reporting history of fever within past 48 hours or other symptoms compatible with malaria and giving their informed consent, will be eligible for the study.

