## 4.3.5 Product used

## Paracheck Pf, Cat No. 30301025, M.L.No 635/L, Lot No. 21071, Mfg. Date May 2004, Exp. Date April 2006, Manufactured by Orchid Biomedical Systems, [name].

### Locality

## The study will be conducted in four different Health facilities (HF) in Zanzibar Islands, two in each Unguja and Pemba Islands. The tentative HFs are: Muyuni (Unguja South District), Uzini (Unguja Central), Kinyasini (Pemba, Micheweni District) and Mzambarauni (Pemba, Wete District). Each study site will enrol patients into both study arms.

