### Serious adverse event definition

A serious adverse event is an adverse event that results in death or is life threatening, an event that requires hospitalization, results in persistent or significant disability or incapacity.

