### Recording of adverse events

Any adverse event (AE) encountered during the course of the study will be reported in the Adverse Events Form.

The intensity of an adverse event will be determined according to the following definitions:

*mild* acceptable, easily tolerated by the patient

*moderate* troublesome (inconvenience in performing normal activities?)

*severe* unacceptable (impossible to perform daily routines?)

*unknown*

The adverse events will also be categorized according to if there is a likely causal relationship between the event and the medical products.

*probably* with respect to time sequence of administration of the drug, unlikely to be attributed to concurrent disease or other drugs or chemicals, and which follows a clinical reasonable response on withdrawal

*possibly* but could be explained by concurrent disease or other drugs or chemicals

*unlikely* with a temporal relationship to the drug administration which makes a causal relationship improbable, and in which other drugs, chemicals or underlying disease provide plausible explanations.

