### Reporting of serious adverse events

If not present at the study site the principal investigator will immediately be informed by phone or fax of any serious adverse events that occur during the study. In addition to the patient’s CRF a separate detailed case report will be prepared. All serious events will be reported, whether or not considered causally related to the study drug. The principal investigator will ensure that all information documented is submitted to the Ministry of Health, Zanzibar.

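### The adverse event definition and causality grades are written for a drug trial, so non-serious deterioration in a patient given no antimalarial, including after a false-negative RDT, is not an adverse event

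*Protocol*

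**What the plan says.** Overall study design (4.3.1) describes a study "comparing RDT + clinical diagnosis versus clinical diagnosis alone in the management of uncomplicated malaria". The only item under Product used is the rapid test, "Paracheck Pf, Cat No. 30301025"; no study drug is named there.

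The safety sections use the vocabulary of a drug trial:

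- **Adverse event definition (4.5.1):** an event must be "temporally associated with the use of the pharmaceutical products in the study", although no causal link has to be shown.
- **Serious adverse event definition (4.5.2):** "A serious adverse event is an adverse event that results in death or is life threatening", or that meets one of the other listed criteria. It takes its scope from 4.5.1.
- **Recording of adverse events (4.5.3):** events are graded on whether there is a "likely causal relationship between the event and the medical products".
- **Reporting of serious adverse events (4.5.4):** "All serious events will be reported, whether or not considered causally related to the study drug".

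The term for the study's pharmaceutical products is not defined anywhere in the protocol.

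**The concern.** The strategy under test is meant to work by reducing the number of patients treated for malaria. Its particular risk is an infection that the test misses, that is left untreated and then worsens. Section 4.4.2 makes this a practical matter: the RDT result is known before treatment, while the microscopy result is kept for the study analysis, so the slide will not alert the clinician to a false-negative test.

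A definition that depends on exposure to a product records the side effects of treatment but has no place for the consequences of withholding it. Coverage then depends on whether a patient was treated, which is the very thing the two arms are expected to differ on.

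**Working it through.** **Reading the sections together.** Take an enrolled patient with a negative RDT who receives no antimalarial and whose fever persists and worsens, without admission to hospital.

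1. Under 4.5.1, no causal link is needed, but use of a product is. On the natural reading of that term as a drug, the event does not qualify.
2. Under 4.5.2, the event is not serious, and a serious event must in any case first be an adverse event.
3. Under 4.5.3, the probable grade refers to the timing of drug administration and the response on withdrawal. The possible grade weighs other drugs or concurrent disease as rival explanations. Even the unlikely grade requires a temporal relation to drug administration. None can be applied to a patient who took no drug.
4. Under 4.5.4, all serious events are to be reported. This conflicts with the nested definition in 4.5.2, but its evident intent is full capture of serious events. It does nothing for the non-serious event above.

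**How many patients are outside the definition.** The protocol gives no figure for this, so what follows is an illustration.

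Inputs:
- Sample size (4.3.4): 103 per group at 4 sites. 103 × 2 × 4 = 824, which reproduces the stated total and gives 824 / 2 = 412 per arm.
- Sample size (4.3.4): a 50% reduction in malaria diagnosis with RDT, taken here as a relative halving of the treated share.
- Introduction: more than 60% of patients at government facilities are diagnosed with malaria. The treated share under clinical diagnosis is therefore assumed to be 60%, with 90% and 100% as alternatives because enrolled patients are selected for symptoms.
- Introduction: RDT sensitivity 97%, specificity 88%.

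Untreated patients = 412 × (1 − treated share):

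| Treated, clinical arm | Treated, RDT arm | Untreated, clinical arm | Untreated, RDT arm |
|---|---|---|---|
| 60% | 30% | 412 × 0.40 = 165 | 412 × 0.70 = 288 |
| 90% | 45% | 412 × 0.10 = 41 | 412 × 0.55 = 227 |
| 100% | 50% | 0 | 412 × 0.50 = 206 |

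**Effect on a table by arm.** Suppose the true event rate is 5% in every patient of both arms, or 412 × 0.05 = 20.6 events per arm. If only treated patients can contribute, the first row gives 412 × 0.60 × 0.05 = 12.4 counted events under clinical diagnosis and 412 × 0.30 × 0.05 = 6.2 under RDT. The ratio is 0.5 whatever the event rate, because it is simply the ratio of the treated shares.

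**False negatives consistent with the first row.** If treatment follows the test, the positive share at prevalence p is 0.97p + 0.12(1 − p). Setting this to 0.30 gives p = (0.30 − 0.12) / 0.85 = 0.21. Expected false negatives are then 412 × 0.21 × 0.03 = 2.6. For the second and third rows the same steps give p = 0.33 / 0.85 = 0.39 and 4.8 false negatives, and p = 0.38 / 0.85 = 0.45 and 5.5.

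**The case against.** Four arguments limit the point.

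**No safety comparison is planned.** A reader might infer that the trial's safety comparison is biased and that it will report RDT as safer. Study objective (4.2) does not support that: it lists treatments prescribed, test accuracy and cost benefit, with no safety endpoint. The tilt arises only if someone tabulates adverse events by arm. It is also not confined to the RDT arm, since untreated patients under clinical diagnosis are outside the definition too. The fault is unequal coverage.

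**The harm is partly visible by other routes.** All patients are told to return if they do not improve or if they deteriorate, and in any case on or after day 14 (Clinical assessment). Treatment at a return visit is evaluated (Duration of study), slides are taken from everyone, and the cost-benefit objective counts revisits due to misdiagnosis. This stands: the protocol would not be blind to missed infections. But these routes record contacts, treatment and cost. They do not ask for the deterioration to be recorded and graded as an adverse event.

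**Serious events are safeguarded.** It would be tempting to say that deaths and admissions of untreated patients go unreported. Section 4.5.4 most naturally means that they are reported, and 4.5.1 itself mentions unscheduled admission among the things its definition could include. The serious-event problem is one of inconsistent wording, probably not of lost events.

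**The key term is undefined.** A patient given some other medicine might be counted as exposed, the RDT itself might be the product meant, and the protocol never says outright that RDT-negative patients go without an antimalarial. All true. But the references in 4.5.3 to administration and withdrawal of a drug point to a drug, the assumed 50% reduction implies that many patients will go untreated, and an ambiguous definition needs correcting as well.

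On size, a reader might take the prevalence of up to 60% quoted for children and arrive at 412 × 0.60 × 0.03 = 7 false negatives. That does not fit with 288 untreated. At 60% prevalence the positive share would be 0.60 × 0.97 + 0.40 × 0.12 = 63%, not 30%.

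**Conclusion.** Sections 4.5.1 to 4.5.3 do not fit a trial of diagnostic strategies, and 4.5.2 and 4.5.4 do not agree with each other. The clear gap is non-serious deterioration in patients who received no antimalarial, in either arm. With 412 per arm, 60% treated on clinical diagnosis and a halving with RDT, about 288 RDT patients and 165 clinical-diagnosis patients lie outside the definition, and about 2 to 3 infected RDT patients would be expected to test negative. These counts rest on an assumed treated share, on treatment following the test, and on the accuracy figures quoted in the Introduction. At treated shares of 90% or 100% the contrast between arms is larger.

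The primary objective and the planned analyses are unaffected. What is at stake is the capture of the harm most specific to the intervention, and the meaning of any adverse event table that may later be produced.

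**What to change.** - **4.5.1:** define an adverse event as any unfavourable sign, symptom or disease that is new or has worsened relative to the presentation at enrolment, in any enrolled patient, from enrolment to the end of follow-up, whether or not an antimalarial was given. The baseline clause is needed because every patient is already symptomatic at enrolment; without it, the presenting illness itself would be counted.
- **4.5.2 and 4.5.4:** make both follow that definition, and remove the reference to a study drug.
- **4.5.3:** keep the drug grades for treated patients and add a relatedness category for the diagnostic decision, meaning treatment withheld or delayed.
- **Reporting:** show any event table by arm and, within arm, by treated or untreated status.

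This changes what is recorded, not how patients are managed. The cost is revised protocol and form wording and more event forms to complete, since untreated patients come into scope. The return visits already in the protocol suffice, so no new visits or staff are needed.

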### Serious adverse event definition

A serious adverse event is an adverse event that results in death or is life threatening, an event that requires hospitalization, results in persistent or significant disability or incapacity.

### Recording of adverse events

Any adverse event (AE) encountered during the course of the study will be reported in the Adverse Events Form.

The intensity of an adverse event will be determined according to the following definitions:

*mild* acceptable, easily tolerated by the patient

*moderate* troublesome (inconvenience in performing normal activities?)

*severe* unacceptable (impossible to perform daily routines?)

*unknown*

The adverse events will also be categorized according to if there is a likely causal relationship between the event and the medical products.

*probably* with respect to time sequence of administration of the drug, unlikely to be attributed to concurrent disease or other drugs or chemicals, and which follows a clinical reasonable response on withdrawal

*possibly* but could be explained by concurrent disease or other drugs or chemicals

*unlikely* with a temporal relationship to the drug administration which makes a causal relationship improbable, and in which other drugs, chemicals or underlying disease provide plausible explanations.

### Reporting of serious adverse events

If not present at the study site the principal investigator will immediately be informed by phone or fax of any serious adverse events that occur during the study. In addition to the patient’s CRF a separate detailed case report will be prepared. All serious events will be reported, whether or not considered causally related to the study drug. The principal investigator will ensure that all information documented is submitted to the Ministry of Health, Zanzibar.

## Bioanalytical assays

Blood slides will be collected from all patients at the field and examination will be done centrally at ZMCP offices in Unguja and Pemba Islands

## Efforts to control investigational procedures

### Monitoring

The principal investigator, the study coordinator and field supervisors will ensure that the facilities for conducting the tests remain acceptable and will ensure that the results of the study are being recorded accurately in the CRFs. There will be no formal monitoring.

### Audits and inspections

Not applicable.

### Training

The principal investigator will ensure that appropriate training relevant to the study is given to Clinician to be able to collect the specimens for further investigation and be well familiarized with the procedure and interpretation of the results of RDT. Any information of relevance to the performance of this study is to be forwarded to the co-investigators and other staff involved.

## Data management and evaluation

### Data management

Data will be entered and managed in a secure computer environment at the ZMCP and ZAMRUKI offices. Data analysis will be performed by ZAMRUKI.

## Publications

Each party shall have the right to publish and disseminate information derived from the performance of work. Qualification for authorship shall be in keeping with generally accepted criteria.

ZAMRUKI/KI shall provide the ZMCP manager with a copy of any proposed publication derived from this study for review prior to submission.

Publications shall carry appropriate acknowledgement of funding support by a statement such as the following: *“This publication was supported financially by organisation X….., its contents are solely the responsibility of the authors and do not necessarily represent the official views of the organisation”.*

## Ethical requirements

### 4.9.1 Declaration of Helsinki and ethical review

The study will be performed in accordance with the principles stated in the declaration of Helsinki. The protocol, including the subject information and informed consent form, will be approved by the Ethics Committee at ZHRC, before enrollment of any subjects into the study. The opinions of the committees should be dated and in writing.

All correspondence with the ethics committees will be filed by the Principal Investigator, who is responsible for informing the committees of any serious adverse events and/or major amendments to the protocol.

### Subject information and consent

The investigator will ensure that each subject, and parent/guardian is given thorough verbal and written information about the nature, purpose, and possible risks of the study. The subjects and their parents/guardians will be informed that they are free to discontinue their participation in the study at any time. The principal investigator is responsible for ensuring that signed and witnessed verbal informed consent is obtained from all subjects and/or parent/guardians before enrollment. Written and verbal information will be given in Kiswahili.

### Changes to protocol and related procedures

No change in the investigational procedures shall be effected without the mutual agreement of the study investigators. All changes must be documented by signed protocol amendments.

**6. Budget:**

**Staff allowances**

2 Supervisors x 70,000/- per week x 8 weeks = 1,120,000/-

2 Laboratory technicians x 50,000/- per week x 8 weeks = 800,000/-

4 Prescibers x 50,000/- per week x 8 weeks = 1,600,000/-

4 Community mobilizers x 25,000/- per week x 8 weeks = 800,000/-

1 Data entry clerks x for 4 weeks = 50,000/-

1 Statistician x 150,000/- = 150,000/-

**Sub Total = 4,520,000/-**

**Laboratory Reagents and other consumable materials**

850 Rapid Diagnostic Tests @600/- per test = 510,000/-

Immersion oil 25ml/bottle x 5,000/- x 10 bottles = 50,000/-

50bxs Microscope slides (76x 25mmfrosted edge) pack of 72x3, 000/- = 200,000/-

Slide carrier (vertical) 30 boxes x 10,000/- = 300,000/-

Methanol (2.5ltrs per bottle) @ 50,000/- x 4 bottles = 200,000/-

Glycerol (2.5 ltrs per bottle) @ 38,000/- x 4 bottles = 152,000/-

20 boxes blood lancets (*pack of 200pcs)* x 5,000/- = 100,000/-

10 rolls Cotton wool (500gm) x 2,500/- per roll = 25,000/-

10 Examination gloves x 4,000/- per box = 40,000/-

10 Liters Methylated spirit @8,000/- = 80,000/-

10tins (25 gms) Giemsa stain powder @ 5,000/- = 50,000/-

8 bottles Xylene (500ml.) @ 5,000/- = 40,000/-

1 binocular Microscope, Olympus CX20 BIMF200 = 1,023,000/-

**Sub Total = 2,260,000/-**

**Stationary (Unguja and Pemba)**

## Photo copying and binding works = 103,000/-

5 rim papers @5,000/- = 25,000/-

1 box black point pens = 5,000/-

8 Counter books@ 3,500/- = 28,000/-

10 box files@3,500/- = 35,000/-

1 rim flip charts@10,000/- = 10,000/-

**Sub Total = 300,000/-**

**Incentive for the patients**

850 ITN x 3,000/- = 2,550,000/-

**Sub Total = 2,550,000/-**

#### Travel costs

Flights tickets ZNZ/PBA/ZNZ = 540,000/-

Flight tickets DSM/ZNZ/DSM = 480,000/-

Night allowances = 450,000/-

**Sub total = 1,470,000/-**

**Transportation**

Renting of field vehicle 30,000/- x 6 trips /week x 8 weeks = **1,950,000/-**

**GRAND TOTAL = 13,050,000/-**

*Annex I:*

## STANDARD OPERATING PROCEDURES (SOP) FOR BLOOD SLIDE COLLECTION AND EXAMINATION

- Laboratory Requirements
- Blood examination for parasites

**Laboratory Requirements:**

- Frosted blood slides
- Cotton wool
- Sterile blood lancets
- Wooden dry rack
- Sharpened pencil
- Examination gloves
- 75% methylated spirit
- Record form or register

**Blood Examination for Parasites:**

- Preparation of thick films

- Labeling of films

- Staining of blood smears

- Examination of films

- Storage of films

**Preparation of thick films:**

- Clean finger with cotton swab soaked in antiseptic (methylated spirit). - Dry with dry cotton wool

- Puncture ball of finger with sterile lancet
- Apply gentle pressure and collect 3 drops (about 1.5 μl) adjacent to each other.
- Using the corner of another slide quickly spread drops of blood to form an evenly spread film of  1 cm in diameter.
- Make two identical films.
- Dry in air or using a hair dryer.
- Label on the frosted edge using a pencil.
- Protect from flies and dust.
- Good thick films should be thin enough to allow a print to be read through.
- Label on frosted end with lead pencil.
- Stain promptly to avoid autofixation

**Staining thick films:**

Stain blood films using the standard method (30min by 3% Giemsa)

**Examination:**

- Count no. of asexual parasites against WBC until 200WBC.
- Complete counting parasites and WBC in the last field even if 200 WBC have been counted, report number of parasites against number of WBC counted.
- If, after 200WBC have been counted, 9 or fewer parasites have been counted, continue counting until you reach 500 WBC, Complete counting parasites and WBC in the last field even if 500 WBC have been counted, report number of parasites against number of WBC counted.
- The number of parasites relative to the WBC count can be converted to parasites per microliter (ul) of blood by the simple mathematical formular : -

Number of parasite/ul of blood = No. Parasites counted x 8,000

No. of WBC

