In June 2004 MSF started an intervention in Unguja South and North A district and Wete district in Pemba within Zanzibar archipelago. The project aims at improving malaria case management; supporting the implementation of the new therapy (arteminsin + amodiaquine) and improving the management of anaemia, lower acute respiratory infections and diarrhoea among under 5 year-old children. The time framework is 18 months.

Nurses issue around 80% of the prescriptions delivered, clinical officers issuing the remaining 20%. When the prescribing person in charge is not present in the HF, non-medical staff members (hospital orderlies) carry out the consultation.

Checks of registration books in the health facilities within South District revealed that, since the new protocol started being implemented in September 2003, there had been a transitional period (from September 2003 to January 2004) when the treatment guideline was not followed consistently.

Rapid diagnostic Test (RDT), based on the detection of antigen derived from malaria parasites, represent a good alternative to microscopy for the diagnosis of *Plasmodium falciparum* malaria (WHO, 1966), in areas lacking resources such as electricity, trained laboratory practitioners and supplies of reagents.

The Para check Pf (dipstick and device) was considered as the most appropriate for the use in the field, being sensitive (97%), moderately specific (88%), easy to use and cheap (about US$ 0.5/test), *Guthmann et.al Trans. of the Royal Soc. TMH (2002) 96,254 -257*

The aim of this study is to evaluate the effect of RDT on the accurate malaria diagnosis and rational use of ACT.

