## Study objective

The primary objective is to compare the proportions of malaria treatments prescribed between two cohorts of clinical diagnosis + RDT and clinical diagnosis alone*.*

Secondary objectives include evaluation of sensitivity, specificity, PPV and PNV of RDT, as well as cost benefit calculations based on reduction of both initial treatment and of revisits due to misdiagnosis.

The selection of the study sites will enable an evaluation of the impact of MSF case management intervention since two out of four sites will already have received “on the job training” on clinical diagnosis through MSF.

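### The RDT targets P. falciparum, but the reference slide is read without a species step, so sensitivity and PNV for P. falciparum may be understated

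*Protocol*

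**What the plan says.** Section 4.2 makes test accuracy a secondary aim: "Secondary objectives include evaluation of sensitivity, specificity, PPV and PNV of RDT". The index test is named under Product used (4.3.5) as "Paracheck Pf, Cat No. 30301025". The Introduction says such tests "represent a good alternative to microscopy for the diagnosis of *Plasmodium falciparum* malaria", and cites the chosen product as "being sensitive (97%), moderately specific (88%), easy to use and cheap".

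The reference is central microscopy. Section 4.4.2 states that "asexual parasite density will be calculated by counting 200 white blood cells". Annex I lists "Preparation of thick films" and describes no thin film. Its Examination step is "Count no. of asexual parasites against WBC until 200WBC", extended to 500 cells when few parasites are found, and the reader reports parasites against white cells counted. Neither place asks for the species. Neither says which slide result counts as positive when the rapid test is judged against it.

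**The concern.** An accuracy table needs the index test and the reference to address the same condition. Here the test is for one species, while the reference, read as written, is positive for asexual parasites of any species. A patient with only a non-falciparum infection and a negative Pf test then lands in the false-negative cell, although the test did what a P. falciparum test should do.

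The sensitivity that the study sets against the cited 97% could therefore look poor because of how the slide was read. A later analysis plan can redefine reference-positive only from what was recorded, and a bare count does not separate a missed P. falciparum infection from a correct negative in another species.

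**Working it through.** **Inputs from the protocol.** Sensitivity 97% and specificity 88% (Introduction); 103 patients per group at each of 4 sites (Sample size). The stated total reproduces: 103 × 2 × 4 = 824, of which 103 × 4 = 412 are in the RDT arm. The protocol sets no precision target for sensitivity or specificity, so there is no planned accuracy figure to reproduce.

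**Assumptions, because the protocol gives no figure.**
- m is the share of slide-positives that are non-falciparum only, taken as 2%, 5% and 10%.
- The Pf test is positive in these patients as often as in slide-negatives, 1 − 0.88 = 0.12.
- Half of the patients are slide-positive.

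**Sensitivity against the slide as read:** 0.97(1 − m) + 0.12m = 0.97 − 0.85m.
- m = 2%: 0.9506 + 0.0024 = 95.3%
- m = 5%: 0.9215 + 0.0060 = 92.75%, or 92.8%
- m = 10%: 0.8730 + 0.0120 = 88.5%

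If the Pf test were never positive in these patients, the formula is 0.97(1 − m), giving 95.1%, 92.2% and 87.3%.

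**All measures, worked for m = 10%.** Take 1,000 RDT patients: 450 with P. falciparum, 50 with another species only, 500 slide-negative.
- RDT positive: 0.97 × 450 + 0.12 × 50 + 0.12 × 500 = 436.5 + 6 + 60 = 502.5
- RDT negative: 13.5 + 44 + 440 = 497.5
- Specificity: 440/500 = 88.0% against the slide as read; (440 + 44)/550 = 88.0% against P. falciparum
- PNV: 440/497.5 = 88.4% against the slide as read; 484/497.5 = 97.3% against P. falciparum
- PPV: 442.5/502.5 = 88.1% against the slide as read; 436.5/502.5 = 86.9% against P. falciparum

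The same steps for the other shares give:

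| m | Sensitivity, slide as read | PNV, slide as read | PNV, P. falciparum | PPV, slide as read | PPV, P. falciparum |
|---|---|---|---|---|---|
| 0 | 97.0% | 96.7% | 96.7% | 89.0% | 89.0% |
| 2% | 95.3% | 94.9% | 96.8% | 88.8% | 88.6% |
| 5% | 92.8% | 92.4% | 97.0% | 88.5% | 88.0% |
| 10% | 88.5% | 88.4% | 97.3% | 88.1% | 86.9% |

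Under these assumptions sensitivity against P. falciparum is 97.0%, and specificity 88.0% against either reference, in every row.

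**Scale against sampling error.** With 412 RDT patients, half slide-positive, 206 enter the sensitivity estimate. The 95% half-width is 1.96 × √(0.97 × 0.03 / 206) = 2.3 points. The shift exceeds this once m passes 2.33/0.85, about 2.7%.

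**The case against.** **The target may be malaria of any species.** The design statement (4.3.1) speaks of uncomplicated malaria without naming a species. On that target, a negative Pf test in a non-falciparum infection is a real miss and the count is the right reference. This stands. The Introduction points to P. falciparum and the design statement does not, which is a reason to report accuracy against both.

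**Silence is not exclusion.** Section 4.4.2 refers to standard microscopy, and the record form and CRF are not shown, so a species field may exist. This stands in part: the Examination step, which is shown, lists what to report and does not include species.

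**The loss is not final.** Two films are made, and slides are labelled by patient and stored (Annex I), so they could be re-read. This stands. Only the recorded counts cannot be corrected.

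**The size is unknown.** P. falciparum is the only species the protocol names, and it gives no share of any other. The reference behind the cited 97% and 88% is not stated either. This stands.

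A reader might go further and infer that gametocyte-only carriers depress specificity, so that all four measures fall. The document does not support this. It says only that the tests are "based on the detection of antigen derived from malaria parasites". It does not say that the product reacts to gametocytes, and it gives no carriage rate. If the test were positive in such patients no more often than in other slide-negatives (12%), specificity would stay at 88.0%. If asexual infection is the target, a positive test in such a patient is a genuine false positive.

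**Conclusion.** The point holds in a limited form. The protocol pairs a P. falciparum test with a slide read that has no species step and does not define reference-positive by species. If non-falciparum mono-infections occur, sensitivity and PNV for P. falciparum are understated. The loss in sensitivity is about 0.85 points for each 1% of slide-positives, provided the test reacts in those patients as in slide-negatives. The shares used are assumptions, and the true effect may be near zero.

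Specificity does not move and PPV rises slightly, so it would be wrong to say that every accuracy measure is biased downwards. One secondary objective is affected. The primary comparison of treatments prescribed does not use the slide and is not affected. This is a cheap improvement, not a flaw that threatens the study.

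**What to change.** In 4.4.2 and in Annex I under Examination:
- Have the reader record the species seen during the same read. Presence of gametocytes can be added as an optional field.
- Define reference-positive for the RDT accuracy analysis as P. falciparum asexual parasites, alone or in a mixed infection.
- List non-falciparum mono-infections in a separate row.
- Also report accuracy against asexual parasitaemia of any species, since the design statement does not limit the target to one.

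The cost is one register field, or two with gametocytes, and a sentence in the SOP, with no extra blood, slide or visit. The downside is that species calls on thick films are less certain at low density, so an undetermined category is needed. If slides have already been read without species, re-reading the stored positive slides from the RDT arm would supply the missing item.
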